#### Blinding and allocation concealment

An independent statistician will generate the randomisation schedule so that the trial statistician remains blinded to group allocation for analysis. Given the design and nature of the quality improvement intervention where CR program staff enter data and use these to improve care, it is not possible to conceal the group allocation from the program staff themselves or the research team delivering the intervention. However, where possible, data collection is conducted blinded to treatment allocation (e.g. data linkage) as well as the statistical analyses.

### Intervention and control groups

#### Intervention Group

CR programs allocated to the intervention arm will participate in a multicomponent, data-driven quality improvement intervention (Table 2). The intervention is designed to use local CR data to drive small, progressive changes using Plan-Do-Study-Act (PDSA) cycles [33] aligned to pre-determined KPIs (Table 1). These indicators have been selected using national and international benchmarks of quality [18–21] and were developed and approved through an iterative process involving the trial investigators, CR clinicians, quality improvement experts, and consumers. The intervention will be guided by the Model for Improvement [34] using streamlined data entry and regular visual reports to programs via purpose-built databases using software systems REDCap and Microsoft PowerBI and underpinned by principles of collaboration and support. CR program leaders will collaborate in an ongoing way over 12 months supported and facilitated by the research team.

**Table 2 Tab2:** Components of the QUICR collaborative quality improvement intervention

1. **QUICR Dashboard and Monthly Reports**
Patient data entered into REDCap will be automatically extracted into a specially developed QUICR Dashboard to generate visual summaries of KPIs assessed and benchmarked against other participating programs anonymously. These monthly reports will provide CR program leaders accurate updates on their program’s performance in relation to KPIs over time.
2. **Collaborative Quality Improvement**
Regular group-based workshops (*n* = 4) (1 in-person and 3 online) will be held to support CR staff in developing quality improvement skills using the Model for Improvement and including PDSA cycles. As part of the collaborative approach, CR program representatives will be assisted to use their local data to identify gaps in best-practice care and initiate program-level changes that can be implemented and tested iteratively over time (Fig. 2). The initial group-based workshop will be six hours long and in-person for all programs in the intervention arm and occur within three months of beginning data collection to ensure reports are available. Workshop dates will be coordinated to minimise work disruption and the research team will support CR program representatives’ travel costs. Subsequent workshops will be three hours long, online, and scheduled every 2–3 months. Data reports for individual CR programs and collated overall performance of the collaborative will be discussed during the workshops and used to identify common areas for improvement. CR program representatives will work together in groups to identify and test potential solutions to shared problems. This collaborative approach will promote mutual learning among CR programs in addressing common issues. Research team members with expertise, skills, and prior experiences in collaborative quality improvement will facilitate all workshops.
3. **Facilitation and Support**
All participating programs in the intervention group will be supported by the research team for all aspects of the trial and the intervention. This team includes personnel trained in delivery of collaborative quality improvement to facilitate interpretation of monthly reports of analysed and visualised data, discuss quality improvement progress and objective feedback on PDSA cycle statements. All participating program staff will also have access to a secure online QUICR trial folder within a SharePoint site hosted by The University of Sydney that will house a suite of QUICR resources to ensure that CR programs have the learning resources they need and support channels to the research team to access in their own time. These resources will include the QUICR handbook, video training for data entry via REDCap and interpreting monthly reports, PDSA cycle worksheets, and frequently asked questions.

#### Control Group

CR programs allocated in the control arm are to provide usual care to their patients. For the purpose of measuring change in primary and secondary outcomes of intervention sites relative to control sites, staff working in CR at control sites are required to enter patient data into the purpose-built REDCap data collection platform. They will not have access to any of the abovementioned QUICR resources. These materials will be provided to the control group following trial completion.

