### Study outcomes

Table 1 outlines the QUICR KPIs. The primary outcome is CR program completion, defined as participation in ≥ 80% of sessions of the usual 6-8-week program. Secondary outcomes include: (1) unplanned hospital admissions, emergency department presentations and deaths, and associated costs via analysis of linked administrative data, (2) proportion of patients receiving guideline-indicated CR according to national and international benchmarks (e.g. assessment of risk factors, exercise capacity, medication adherence, and HRQL at entry and completion, and documented discharge transition plan), and (3) enablers and barriers to implementation of the QUICR intervention.

**Table 1 Tab1:** QUICR Key Performance Indicators

1. Program completion
2. Wait time
3. Exercise capacity
A. Proportion of patients assessed for exercise capacity scores at initial assessment
B. Proportion of patients assessed for exercise capacity scores at completion assessment
C. Proportion of patients achieving improvement in exercise capacity
4. Low-density lipoprotein cholesterol (LDL-C)
A. Proportion of patients checked for LDL-C
5. Medication adherence
A. Proportion of patients assessed for medication adherence at initial assessment
B. Proportion of patients currently adhering to medication regimen at initial assessment
C. Proportion of patients assessed for medication adherence at completion assessment
D. Proportion of patients currently adhering to medication regimen at completion assessment
E. Change in proportion of patients currently adhering to medication regimen
6. Smoking
A. Proportion of patients assessed for smoking at initial assessment
B. Proportion of patients currently smoking offered/referred for smoking cessation counselling
C. Proportion of patients assessed for smoking at completion assessment
D. Proportion of patients currently smoking
E. Change in proportion of patients currently smoking
7. Depression
A. Proportion of patients screened for depression at initial assessment
B. Proportion of patients positive for depression offered/referred for counselling
C. Proportion of patients screened for depression at completion assessment
D. Proportion of patients positive for depression at completion assessment
E. Change in proportion of patients positive for depression
8. Health-related quality of life (HRQL) using EQ-5D-5 L
A. Proportion of patients assessed for HRQL at initial assessment
B. Proportion of patients assessed for HRQL at completion assessment

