### Data Collection and Management

All data will be collected at baseline, 12, and 24 months. The primary endpoint is 12 months. Individual patient-level data will be collected by CR program staff as part of routine care. De-identified demographic and CR patient outcomes data including costs will be entered into a purpose-built login-protected REDCap data collection platform hosted by the University of Sydney [35]. The master coding sheet with full patient identifiers will remain at each CR site’s server and will be the responsibility of the data custodian nominated at each program. Coding is crucial for this trial to enable access to and analyse administrative data for linkage. Data extracted to the QUICR Dashboard will be aggregated and automatically converted to visual form and no individual data point will be traceable. The QUICR Dashboard will also be login-protected, to which only a select number of the research team will have access.

Unplanned hospital admissions, emergency department presentations, and deaths will be collected via state-based linked administrative data. Probabilistic matching will be used to link records and the estimated proportion of invalid and missed links using data linkage is expected to be very low [36]. 

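### Control programs must enter the primary outcome in REDCap but are barred from the trial's REDCap data-entry training and support, so recording can differ by arm and bias the comparison in an unknown direction

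*Protocol article*

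**What the plan says.** The Control Group section states that "staff working in CR at control sites are required to enter patient data into the purpose-built REDCap data collection platform", and gives the reason: to measure change in the primary and secondary outcomes relative to the intervention sites. It continues: "They will not have access to any of the abovementioned QUICR resources", and then "These materials will be provided to the control group following trial completion".

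The resources are described in Table 2 (Intervention Group section), under the third component, Facilitation and Support: "These resources will include the QUICR handbook, video training for data entry via REDCap and interpreting monthly reports". The same list adds worksheets for Plan-Do-Study-Act (PDSA) cycles and frequently asked questions, and the online folder also offers support channels to the research team. Research-team help is promised to one arm and extends beyond quality improvement: "All participating programs in the intervention group will be supported by the research team for all aspects of the trial and the intervention".

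On the outcome, the Study outcomes section says: "The primary outcome is CR program completion, defined as participation in ≥ 80% of sessions of the usual 6-8-week program". On who records it, Data Collection and Management says: "Individual patient-level data will be collected by CR program staff as part of routine care". The section on blinding accepts that program staff know their allocation. The only blinded data collection it names is data linkage, which supplies admissions, emergency presentations and deaths, not completion.

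**The concern.** Table 2 bundles two kinds of material. One is the intervention: handbook, dashboard and reports, PDSA worksheets, workshops, facilitation. The other is measurement: how to enter data in REDCap, and where to get help with it. The Control Group section withholds the whole bundle. The process that produces the primary outcome therefore differs by arm, by a stated rule.

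Besides completion, many of the Table 1 indicators are proportions of patients assessed, checked or screened (3A, 3B, 4A, 5A, 5C, 6A, 6C, 7A, 7C, 8A, 8B), and 10A is the proportion who completed a survey. For these, an assessment that was done but not entered can look the same as one not done. If one arm is better trained in data entry, part of any difference on these measures may reflect recording and not care. A blinded statistician and a model that allows for clustering cannot remove misclassification that depends on arm.

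**Working it through.** **Reading the passages together**

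1. Control staff must enter outcome data in REDCap (Control Group).
2. REDCap data-entry training is one of the QUICR resources (Table 2, third component).
3. Control programs get none of those resources until the trial is over (Control Group).
4. Hence, as written, control staff enter the primary outcome without the trial's data-entry training, and intervention staff enter it with that training.
5. Program Eligibility Criteria requires REDCap proficiency at every program. That concerns the platform. It does not cover the trial's forms or how the 80% rule is applied to them.

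**The plan's own figure**

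Inputs from the Sample size section: 20 programs per arm, 33 patients each (660 per arm), 59% control completion, an increase of 22% read as 22 percentage points (to 81%), intraclass correlation 0.29, alpha 0.05 (two-sided assumed).

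- Design effect = 1 + (33 − 1) × 0.29 = 10.28
- Effective sample per arm = 660 / 10.28 = 64.2
- Standard error = √[(0.59 × 0.41 + 0.81 × 0.19) / 64.2] = 0.0785
- Power = Φ(0.22 / 0.0785 − 1.96) = Φ(0.84) = 80.0%

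The stated 80% reproduces, so the same effective sample size can be used for an illustration.

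**Illustration A: control completions under-recorded**

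Assumptions, none of them from the document: true completion is 59% in both arms, recording is complete in the intervention arm, and a fraction f of true control completions is unrecorded and counted as non-completion.

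- Spurious difference = 0.59 × f
- Null standard error = √(2 × 0.59 × 0.41 / 64.2) = 0.0868

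| f | Spurious gain | Shift in standard errors | Two-sided rejection probability |
|---|---|---|---|
| 0 | 0 | 0 | 5% |
| 5% | 0.0295 (3.0 points) | 0.34 | P(Z > 1.62) + P(Z < −2.30) ≈ 6% |
| 10% | 0.059 (5.9 points) | 0.68 | P(Z > 1.28) + P(Z < −2.64) ≈ 10% |

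At f = 10% the spurious gain is 5.9 / 22 = 27% of the target difference.

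**Illustration B: control non-completers under-entered**

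Same true rate, but now 10% of control non-completers never reach the dataset, and everyone else is recorded correctly.

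- Non-completers entered = 0.41 × 0.90 = 0.369
- Apparent control completion = 0.59 / (0.59 + 0.369) = 61.5%
- Bias = 59% − 61.5% = −2.5 points, against the intervention

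The sign of the bias therefore depends on which records are lost and how missing ones are handled.

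**The case against.** - **The mechanism is not documented.** The article does not say whether REDCap takes session-by-session attendance, a session count or a completion flag set by staff, nor how unrecorded sessions are treated. The handling of missing data commonly belongs to the analysis plan, which is not shown. This stands, and it is why neither size nor direction can be fixed.
- **Other provisions lower the risk.** All programs must be REDCap-proficient, and patient data come from routine care. Both should narrow any gap between arms. Neither trains staff in this trial's fields.
- **Folder access could be read as covering both arms.** Table 2 says "All participating program staff will also have access to a secure online QUICR trial folder". But the sentence sits in a table of intervention components, and the Control Group section excludes that reading.
- **The article is a condensed source.** Control sites may get form instructions under the full protocol, so a reader should not infer that they receive none at all. If they do receive them, the sweeping exclusion in the Control Group section is loose drafting and still needs correcting.
- **A reader might infer that the intervention arm's monthly reports expose incomplete entry.** Table 2 describes summaries of indicators and benchmarking, not data-completeness checks, so that is an inference and the point does not rest on it.

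**Conclusion.** The point holds as a defect in a stated rule: data-entry training and support are tied to the intervention and withheld from the arm that serves as comparator, while unblinded staff in both arms record the primary outcome. Recording can differ by arm and bias the comparison.

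The illustrative range is a spurious gain of 3.0 to 5.9 points, with type I error of about 6% to 10%, if 5% to 10% of control completions are lost and counted as non-completion. In the other direction it is about 2.5 points against the intervention, if 10% of control non-completers are not entered. These rates are assumptions.

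Two stronger readings are not supported. One is that the bias must favour the intervention: illustration B shows the reverse is possible. The other is that the trial would measure data entry and not completion: even the 10% case accounts for only 5.9 of the 22 target points, and the document gives no recording rate. Confidence is medium. The change is worth making because it costs little.

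**What to change.** Amend the Control Group section, and Table 2 to match, so that the resource bundle is split:

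- **Both arms, identical:** REDCap data-entry video training, field definitions including how the 80% rule is applied, data-entry FAQs and a data-entry helpdesk.
- **Intervention arm only until the trial ends:** handbook, dashboard and indicator reports, training in interpreting reports, PDSA worksheets, workshops and facilitation.

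Do not add monthly completeness queries on the indicator assessment fields for control sites. Telling a site each month that its assessment fields are blank comes close to feeding back the proportion-assessed indicators, and data feedback is part of the intervention. Any data query should be identical in both arms and limited to primary-outcome fields.

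The training video and FAQs already exist, so the cost is mainly folder permissions, a short field guide and opening data-entry help to both arms. The downside is slightly more trial contact in the control arm. If control sites already receive this training under the full protocol, only the wording needs correcting.

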**Fig. 2 Fig2:**
[figure not shown]
QUICR PDSA Diagram

### Data Collection and Management

All data will be collected at baseline, 12, and 24 months. The primary endpoint is 12 months. Individual patient-level data will be collected by CR program staff as part of routine care. De-identified demographic and CR patient outcomes data including costs will be entered into a purpose-built login-protected REDCap data collection platform hosted by the University of Sydney [35]. The master coding sheet with full patient identifiers will remain at each CR site’s server and will be the responsibility of the data custodian nominated at each program. Coding is crucial for this trial to enable access to and analyse administrative data for linkage. Data extracted to the QUICR Dashboard will be aggregated and automatically converted to visual form and no individual data point will be traceable. The QUICR Dashboard will also be login-protected, to which only a select number of the research team will have access.

Unplanned hospital admissions, emergency department presentations, and deaths will be collected via state-based linked administrative data. Probabilistic matching will be used to link records and the estimated proportion of invalid and missed links using data linkage is expected to be very low [36]. 

### Sample size

A sample of 40 CR programs (20/arm) with 33 patients with CHD in each program (660 patients/arm), will achieve 80% power to detect an increase in the CR completion rate of 22% from 59%. The control proportion estimated is 59% from our Australian National Cardiac Rehabilitation Quality Benchmark study (*n* = 2,436; 39 programs) [37]. The estimated change in completion rate is based on US data (*n* = 1103) reporting 25% increase in completions from quality improvement interventions [27]. We anticipate a slightly reduced effect as we are not using their small financial incentives. The intraclass correlation is 0.29, based on a cross-sectional study of cardiac rehabilitation [27]. The significance level of the test is 0.05.

### Statistical analyses

A study statistician blinded to the group allocation will lead all analyses according to a prespecified statistical analysis plan following intention-to-treat principles and consider CR program clustering. Descriptive statistics will be calculated and used to characterise patients, programs and KPIs. Mixed-effects linear and logistic regression models will be used for continuous and binary outcomes, respectively, accounting for clusters within the trial. Mixed-effects regression analysis adjusting for imbalances in patients at baseline will be conducted as sensitivity analysis. Prespecified subgroup analyses will be performed for gender, urban/regional CR sites, program size and duration, and private, public and community-funded programs. A detailed analysis plan will be developed and signed off prior to unblinding.

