### Randomization

Each CR program will be randomized 1:1 to intervention (QUICR) or control group, via a computer-generated sequence allocation using simple randomization. CR programs that closely interact with each other were treated as a single cluster to circumvent the likelihood of contamination. Allocation will be stratified 50:50 by location of the programs (urban and regional areas) using SAS v9.4.

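### The described analysis leaves the stratification factor out of the model and confines covariate adjustment to a sensitivity analysis whose covariates are picked by observed patient-level imbalance

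*Protocol article*

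**What the plan says.** The Randomization section of the protocol article makes location a stratification factor: "Allocation will be stratified 50:50 by location of the programs (urban and regional areas". The same section calls the sequence simple randomization and says that programs in close contact are merged into one cluster.

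The Statistical analyses section names mixed-effects logistic regression for binary outcomes, which covers the primary outcome of program completion. Clustering is the only feature of that model it states. It then adds: "Mixed-effects regression analysis adjusting for imbalances in patients at baseline will be conducted as sensitivity analysis". Location appears in that section only in the list of subgroups. A detailed analysis plan is to be signed off before unblinding.

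Two other sentences bear on baseline data. Data Collection and Management says "All data will be collected at baseline, 12, and 24 months". The Control Group section explains why control staff enter data: "For the purpose of measuring change in primary and secondary outcomes of intervention sites relative to control sites". Neither describes a completion rate for each program from before the intervention.

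**The concern.** Three features of the described analysis fit the design poorly.

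- **The stratum is not in the model.** If location predicts completion, a model without it leaves that variation in the residual between-program variance. The standard error is then larger than it need be. Where stratification has in fact balanced location, the error is conservative.
- **The covariates are chosen by looking.** Selecting those that happen to differ between arms leaves the adjusted model undefined until the data are seen. It also rewards imbalance rather than prognostic strength: a strong predictor that is balanced stays out, and a weak one that differs by chance goes in.
- **The adjustment is at patient level.** Programs are randomized, and the plan assumes a high intraclass correlation. Chance differences between about 40 programs are the main source of error, and patient covariates reach them only through case mix.

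At stake is precision in a trial sized for a difference as large as 22 points, together with a clear advance statement of the adjusted analysis.

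**Working it through.** **Inputs (Sample size section).** "A sample of 40 CR programs (20/arm) with 33 patients with CHD in each program (660 patients/arm), will achieve 80% power"; control rate 59%; an increase of 22%, read as 22 percentage points (to 81%); significance level 0.05, taken as two-sided; and "The intraclass correlation is 0.29, based on a cross-sectional study of cardiac rehabilitation".

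**Step 1. Reproduce the design.**
- Design effect = 1 + (33 − 1) × 0.29 = 10.28.
- Unpooled variance term = 0.59 × 0.41 + 0.81 × 0.19 = 0.3958.
- n per arm if independent = 0.3958 × (1.960 + 0.842)² / 0.22² = 64.19; times 10.28 = 659.8, against 660 stated.
- Standard error = √(0.3958 × 10.28 / 660) = 0.0785, so power = Φ(0.22/0.0785 − 1.96) = 0.800.

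The plan's figure is reproduced with no covariates. The pooled-variance version of the test, with 660/10.28 = 64.2 effective patients per arm, gives 0.783. A t reference with 38 degrees of freedom gives 0.780. The comparisons below start from 0.783.

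**Step 2. Where the variance lies.** Between-program share of the variance of a program's rate = 0.29 / (0.29 + 0.71/33) = 0.931. Patient covariates act directly on the remaining 7%.

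**Step 3. Location in the model.** The documents do not say how much between-program variance location explains, so the share s is assumed. Variance factor = 1 − s × 0.931.
- s = 0.02: factor 0.981, power 0.791
- s = 0.05: factor 0.953, power 0.802
- s = 0.10: factor 0.907, power 0.822
- s = 0.20: factor 0.814, power 0.861

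**Step 4. A baseline completion rate, if one existed.** Assume different patients in each period, 33 baseline patients per program, and a correlation ρ between a program's underlying rates in the two periods. Then r = ρ × 0.931 and the variance factor is 1 − r². The detectable difference is 0.220 × √factor.

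| ρ (assumed) | Variance factor | Power | Detectable difference |
|---|---|---|---|
| 0.3 | 0.922 | 0.816 | 0.211 |
| 0.5 | 0.783 | 0.874 | 0.195 |
| 0.7 | 0.575 | 0.953 | 0.167 |
| 0.8 | 0.445 | 0.985 | 0.147 |

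With 12 baseline patients per program (assumed), the factors at ρ = 0.5, 0.7 and 0.8 are 0.807, 0.621 and 0.505.

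**Step 5. How large a baseline cohort the timetable allows.** The first workshop falls within three months (13 weeks) of the start of data collection, and a program lasts 6-8 weeks. If it falls at three months, only patients enrolled in the first 5-7 weeks can finish before it. At the eligibility minimum of 70 patients a year, or 1.35 a week, that is about 7-9 per program, and fewer with coronary heart disease. With 8 patients, r = ρ × 0.29 / √[(0.29 + 0.71/33)(0.29 + 0.71/8)] = ρ × 0.844, so the factors at ρ = 0.5 and 0.7 are about 0.82 and 0.65. Larger programs would have more patients.

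**The case against.** The best reply is that this is material for the analysis plan. The article defers to a prespecified plan, names no fixed effects at all (not even treatment), and so does not state that location is excluded. An unadjusted clustered analysis is valid, a conservative standard error does not inflate the type I error, and the power claim holds.

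Most of that stands, and it limits the point. It does not remove it. The article does more than stay silent: it assigns covariate adjustment to a sensitivity analysis and states the rule for choosing covariates. The natural reading is an unadjusted primary model, and an analysis plan faithful to the text would carry both choices over.

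Three stronger readings are tempting and are not supported.

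- A reader might infer that the primary model itself adjusts for whatever imbalances appear. The text places that rule in the sensitivity analysis only.
- A reader might infer from the baseline collection and the stated aim of measuring change that a baseline completion rate is available and has been ignored. Completion means attending at least 80% of the sessions of a 6-8-week program, so a patient has no baseline value. No pre-intervention cohort is described. Early data collected after randomization could make such a rate a post-randomization covariate; the article does not settle the timing.
- A reader might infer that a large precision gain is being given away. That needs a correlation of about 0.7 or more, which the documents do not give; at 0.3 the variance falls by only 8%.

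The variance factors also apply to differences in program rates. They carry over only approximately to a mixed logistic model, in which adjustment changes the odds ratio being estimated.

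**Conclusion.** The point holds as one of efficiency and pre-specification. Location is used to stratify allocation but is not named in the described model, and the only adjustment described is driven by the data and aimed at patients, when about 93% of the variance of a program's rate lies between programs. The 93% rests on the plan's own intraclass correlation and cluster size.

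The size of the gain rests on assumptions. Location alone probably gives a modest one: power of about 0.79-0.86 from 0.783 if it explains 2-20% of between-program variance. Adjusting for a baseline rate would cut variance by about 8-55% for correlations of 0.3 to 0.8 with 33 baseline patients per program, and by less with a smaller cohort. That second gain is available only if a suitable rate exists. There is no error in the stated sample size or power, and no threat to the validity of the primary test has been shown.

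**What to change.** Before unblinding, settle the following in the analysis plan and align the Statistical analyses text with it.

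1. Primary model: mixed-effects logistic regression with treatment and location stratum (urban or regional) as fixed effects and a random intercept for the randomized cluster. Merged programs count as one cluster.
2. Replace adjustment for imbalances with a short list of prognostic covariates fixed in advance, for example age and sex.
3. Keep the unadjusted model as a sensitivity analysis.
4. Add each program's completion rate to the primary model only if a rate from before the intervention, ideally before randomization, is available for every program. State its source and time window.

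The cost is wording plus one degree of freedom for location and one more for a baseline rate, among about 40 clusters (fewer where programs were merged). The adjusted odds ratio is conditional on the covariates and will differ from the unadjusted one, so the plan should say which is the headline estimate.
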